### Handling Missing Data

If there are missing data, they will be reported for each variable and missingness mechanism will be explored. Missing values could depend on other observed data. We will consider these missing values as missing at random (MAR). If there is no correlation between the missing values and other observed data (i.e., the Little's test is not statistically significant, *p* > 0.05) missing values will be considered missing completely at random (MCAR) (20). If missing values are MAR, a series of multiple imputations by chained equations will be performed and the Rubin's rules will be used to combine variable estimates and standard errors (21). If missing values are MCAR, complete case analysis will be performed.

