### Primary Outcome

The primary outcome will be the difference in the proportion of patients with good outcomes as defined by a mRS score of 2 or less at 90 days.

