### Sample Size Estimates

A sample size of 280 subjects in each arm achieves 80% power to detect treatment differences of 14% between the intervention and the control groups, using a two-sided binomial test at significance level of 0.05, assuming that 40% of the control patients will experience good outcome defined by a mRS score of 2 or less at 90 days, and allowing a misdiagnosis rate of 29% (15% of haemorrhagic strokes and 14% of mimic stroke conditions). Two extra interim analyses will be performed at 33 and 67% of recruitment on the primary outcome. Early stopping is planned if large differences between the study groups are observed in order to reduce study participants' exposure to the inferior study arm and saving time and resources. Since repeated significance testing on accumulating data will be performed, adjustment of the usual hypothesis testing procedure to maintain the overall significance level of 0.05 will be done by using the flexible type I error spending function (18, 19). Due to the interim analyses, the sample size must be increased by an inflation factor of 1.02, resulting in 572 patients (286 per group).

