### Statistical Analyses

Included patients will be described with respect to demographic and clinical characteristics, according to the study arm. Continuous variables will be summarized using means and standard deviations for normally distributed data; or median and 25–75% percentiles for non-normally distributed data. Normal distribution will be assessed by means of the Shapiro–Wilks test, rejecting normality when *p* <0.05. Categorical data will be summarized using counts and percentages. Comparisons will be performed by means of the Pearson's chi-squared test for categorical variables; the *t*-test for normally distributed data; and the Mann–Whitney *U*-test for non-normally distributed data.

Primary analysis will be performed by means of the binomial test. If the study groups are unbalanced, the primary outcome will be compared using a logistic regression model that will include the variables exhibiting baseline differences as covariates.

Secondary outcomes will be compared using the most appropriate test according to the distribution of the data. As with the primary analysis, secondary outcomes and safety outcome analyses will be conducted using multivariable generalized linear models with suitable links.

The analysis will be performed on the intention-to-treat set and will be repeated on the per-protocol set as a sensitivity analysis.

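### A non-significant Little's test does not establish MCAR and should not switch the analysis to complete cases

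*Protocol article*

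**What the plan says.** Under Handling Missing Data, the protocol article first concedes that "Missing values could depend on other observed data" and says such values will be treated as missing at random (MAR). It then makes the method depend on a test. If "the Little's test is not statistically significant" (p > 0.05), the values are classed as MCAR. Each class has its own analysis: "If missing values are MAR, a series of multiple imputations by chained equations will be performed", but "If missing values are MCAR, complete case analysis will be performed".

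The outcome most affected is the primary one, the "difference in the proportion of patients with good outcomes as defined by a mRS score of 2 or less at 90 days". Under Statistical Analyses it is compared by a binomial test, with covariates added only if the groups are unbalanced. The same section states that "The analysis will be performed on the intention-to-treat set".

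**The concern.** A p-value above 0.05 shows only that the data did not contradict MCAR strongly enough to reject it. With few missing outcomes, that is the likely result even when loss does depend on prognosis. The test also looks only at observed variables, so it cannot speak to loss that depends on the 90-day mRS itself.

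The rule therefore lets a weak pre-test overturn the plan's own starting assumption of MAR and replace imputation with deletion of incomplete cases. The choice is made after the data are seen. It also depends on which variables enter the test, because each uninformative variable added lowers its power. What is at stake is bias in the primary risk difference, which the default unadjusted comparison would not correct.

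**Working it through.** **Inputs from the article.** N = 572 (286 per arm); control rate 40%; target difference 14 points, so 54% under RIPerC; Little's test cut-off 0.05.

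**The plan's own figure.** Without continuity correction, n per arm = [1.96·√(2·0.47·0.53) + 0.842·√(0.40·0.60 + 0.54·0.46)]² / 0.14² = 198.3, so 199. Then 199/0.71 = 280.3 and 280.3 × 1.02 = 285.9, which matches the stated 280 and 286. The sample size reproduces, and nothing below depends on it.

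**Assumed inputs.** The article states no missing rate, no severity gap and no list of tested variables. I take 3-10% missing, missing patients worse by d = 0.3-0.5 SD on one variable, and K = 3 or 10 variables in the test.

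**Step 1: power of the test.** With n1 missing and n0 observed, the statistic is approximately non-central chi-square on K degrees of freedom with non-centrality λ = (n1·n0/N)·d². The 5% critical values are 7.81 (K = 3) and 18.31 (K = 10). Example: 5% missing gives n1 = 28.6 and n0 = 543.4, so n1·n0/N = 27.17; with d = 0.4, λ = 27.17 × 0.16 = 4.35.

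| Missing | d | λ | Power, K = 3 | Power, K = 10 |
|---|---|---|---|---|
| 3% | 0.3 | 1.50 | 0.153 | 0.101 |
| 5% | 0.4 | 4.35 | 0.387 | 0.233 |
| 10% | 0.4 | 8.24 | 0.668 | 0.448 |
| 10% | 0.5 | 12.87 | 0.867 | 0.678 |

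The range is about 10% to 87%.

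**Step 2: cross-check by simulation.** Little's test was simulated 800 times per setting, with N = 572, or 406 (the 71% expected to have ischemic stroke), and 3 or 10 variables. Missingness depended on severity, with or without an additional arm effect of the same odds ratio. The table shows how often the rule selects complete-case analysis although the data are not MCAR.

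| Odds ratio of missingness per SD | 3% missing | 5% missing | 10% missing |
|---|---|---|---|
| 1.5 | 71-88% | 52-84% | 24-70% |
| 2 | 28-73% | 7-52% | 0-21% |

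**Step 3: bias in the risk difference.** The probability of a good outcome, π(x), is taken to fall with standardised severity x at a log-odds slope of 1.2 (assumed), with intercepts set to give 40% and 54%. With m(x) the probability of being missing, the complete-case rate in an arm is E[(1 − m(x))·π(x)] / E[1 − m(x)]. Integrating over a standard normal x at 10% missing:

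| How loss depends on severity | Sham | RIPerC | Difference | Bias (points) |
|---|---|---|---|---|
| Same in both arms, OR 2 | 41.41% | 55.54% | 14.13 | +0.13 |
| Same slope, OR 2, plus arm effect OR 2 | 41.01% | 55.98% | 14.97 | +0.97 |
| Opposite slopes, OR 1.5 | 39.08% | 54.93% | 15.85 | +1.85 |
| Opposite slopes, OR 2 | 38.46% | 55.54% | 17.08 | +3.08 |

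The simulation agrees: at most about 1 point at up to 10% missing when severity acts alike, and 1.5-3.1 points at 10% (0.8-1.9 at 5%) with opposite slopes. Monte Carlo error is about 0.2 points for bias and at most 1.8 points for proportions.

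**Step 4: does the test see the harmful case?** With opposite slopes, missing and observed patients look similar in mean severity once the arms are pooled. Little's test was non-significant in 90-96% of those trials, against 94-96% when the data really were MCAR. It barely tells the two apart.

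**The case against.** The strongest reply is that low power and material bias mostly do not coincide. In the setting with 23% power (5% missing, 0.4 SD, K = 10), severity acts alike in both arms, the two rates shift together, and the bias is about 0.03 points (0.06 at 10% missing). Bias matters only when loss relates to prognosis differently by arm, and exactly opposite slopes are a constructed extreme. This stands, and it limits the size of the point.

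Three stronger readings are tempting, and the document does not support them.

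- A reader might infer that the rule usually picks a biased method. The article gives no missing rate, severity gap or variable list. At 10% missing with an odds ratio of 2, the test misses the dependence in only 0-21% of trials.
- A reader might illustrate the harm with one-sided loss: 10% missing under RIPerC with 30% good outcomes and none missing under sham gives (0.54 − 0.10 × 0.30)/0.90 = 56.7%, a bias of 2.7 points. If arm is among the tested variables, the rule would catch this. Arm would differ by (1 − 257.4/543.4)/0.5 = 1.05 SD, so λ = 27.17 × 1.05² ≈ 30, and power is about 98% at K = 10.
- A reader might see a contradiction with the intention-to-treat statement. That sentence names the analysis set, while the missing-data section says how gaps within it are handled. Complete-case handling weakens an intention-to-treat analysis, but the two sections do not contradict each other.

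The imputation predictors, the scoring of deaths and any not-at-random analysis may properly be left to the full protocol or SAP, and their absence from an article is no defect. None of this rescues the inference from a non-significant test to MCAR, which the article states outright.

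**Conclusion.** The concern holds in a limited form. The article fixes a rule that treats p > 0.05 on Little's test as establishing MCAR and switches to complete-case analysis on that basis. The inference is invalid whatever the missing rate proves to be. How often it misleads depends on assumptions: detection runs from about 10% to 87% over the ranges used here.

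The effect on the primary contrast is at most about 1 point at up to 10% missing if severity drives loss alike in both arms. With opposite relations by arm it is about 1.5-3 points at 10% missing, roughly a tenth to a fifth of the 14-point target (1.5/14 = 0.11; 3/14 = 0.21). In that situation the switch gives almost no protection. These bias figures also rest on the assumed outcome slope of 1.2. The point should be corrected, but it does not show that the trial's result would be wrong.

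**What to change.** Delete the Little's test switch from Handling Missing Data. State that missing 90-day mRS will be handled by the multiple imputation under MAR that the section already names, carried out by arm, whatever any test of MCAR shows. Keep complete-case analysis as a sensitivity analysis. Little's test may still be reported descriptively. A delta-adjusted, not-at-random sensitivity analysis would be a useful optional addition, since neither branch of the present rule addresses loss that depends on the unseen outcome.

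The cost is a wording change and a little more analysis work. Sample size and trial conduct are unaffected.

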### Current Status of the Trial

The study started recruitment in August 2019 in one Hospital, and the estimated completion date is August 2022. At 1st August 2020: 76 patients have been recruited.

## Discussion

RIPerC emerges as an interesting neuroprotective strategy (5). Our study improves the previous limited experience in humans (8, 11). It includes all AIS with symptom onset within 8 h and not only intravenous alteplase treated patients (11). According to the animal model, it is effective when applied both alone and in combination with revascularization therapies (22, 23). Although few studies have been published about the effect of RIC in AIS, some important issues have been learned (8–11). As in Hougaard's trial (11) and in most of the trials involving patients with myocardial infarction (7, 24) it is applied it in the ambulance, as soon as possible, in order to induce the maximum effect. This action seems to be safe although the definitive diagnosis will not be established until the arrival at the hospital. To date, no serious adverse effects have been reported in RIC studies (5, 7–11, 25). The recent RCT published by Pico et al. failed to demonstrate an effect of RIC in the final infarction size in AIS. One explanation of their neutral results was that the treatment with RIC was performed too late during or after the receipt of reperfusion therapies (10). In addition, we will increase the number of cycles to five. Most RIC trials use the four-cycle protocol (7, 11) due to tradition. The ischemic conditioning phenomena was first demonstrated using this protocol in an animal model of myocardial infarction (26). Recent studies in animal models address the need to increase the number of cycles in order to optimize the efficacy of RIPerC (27). Some other recent successes in remote ischemic preconditioning (28) and chronic postconditioning (29) in AIS patients have used the 5-cycle protocol. Increasing the duration of the cycle to 10 min does not offer any further protection (27). Although the quantity of muscle mass affects the efficacy of the intervention, we decided to perform the RIPerC on an upper arm rather than on a leg for safety reasons as up to one in four AIS patients have silent peripheral arterial disease defined by a low ankle-brachial index (30). One of the main shortcomings of the previously mentioned Hougaard's trial (11) was that fewer than one out of three patients complete the four cycles of limb ischemia. We will therefore use an automatic device. To avoid misdiagnosis only subjects with RACE score of >0 and RACE motor items >0 will be included. Finally, according to the stroke treatment academic industry roundtable (STAIR) recommendations a clinical endpoint would clearly evaluate the utility of applying RIPerC in AIS patients.

## Summary and Conclusions

RIPerC represents a new paradigm in neuroprotection with limited data in AIS patients. According to previous preclinical and clinical studies of acute ischemia, a clinical RIPerC trial should include both candidates and non-candidates for reperfusion therapies. As the RIPerC effect decreases with time, RIPerC should be started during the transfer of stroke code patients. The size of the trial should be large enough to detect differences in clinical outcomes and not only neuroimaging endpoints. Finally, the RIC device should be automatic to not only ensure that patients finish all of the programmed cycles but also to interfere as little as possible with the work of paramedics during the transfer and of nurses and physicians during the admission.

## Ethics Statement

The studies involving human participants were reviewed and approved by the Ethics Committee on Clinical Research of the Hospital Universitari Arnau de Vilanova de Lleida. The patients/participants provided their written informed consent to participate in this study.
